## 7.6 Visits after W96

All patients remain in the trial until the last patient enrolled has completed the W96 visit. Follow-up visits after W96 should be scheduled every three to four months and procedures performed according to standard of care. At every follow-up visit, the following assessments and procedures are performed:

- medical history and adverse events since the last visit
  - medication history since the last visit
  - recording of contraceptive methods in women
  - blood sample for local laboratory assessments
- laboratory assessments:
- plasma HIV-1 RNA
  - CD4+ T-cells
  - complete blood count
  - Other laboratory assessments as standard of care
- study drug dispensation for those patients having not reached the end of the trial (defined as the last patient's W96 visit)

Data collected at follow-up visits after W96 need to be recorded on the case report forms. Visits after W96 are identified by months of follow-up (FU-M) and not weeks.

## **7.7 Assessment of safety**

The following procedures aim at assessing safety during the trial (see paragraph 7.5 for schedule of assessments):

- Recording of current medical conditions, HIV-associated conditions, AEs, SAEs and SUSARs (see chapter 9 for reporting of AEs, SAEs, and SUSARs)
- Medication reporting
- Complete physical examination: vital signs, body weight, general appearance, eyes, ears/nose/throat, cardiovascular, respiratory, gastrointestinal, neurological, musculoskeletal, skin, other. Weight is measured at each visit, the patient being nude or wearing underwear only). Systolic and diastolic blood pressure is also assessed at each visit. Physical examination is targeted according to presenting signs and symptoms.
- Measurement of hip and waist circumference
- Laboratory assessments (hematology, clinical chemistry, urine analysis, estimated glomerular filtration rate)

## **7.8 Assessment of efficacy**

The following procedures aim at assessing efficacy during the trial (see paragraph 7.5 for schedule of assessments):

- Laboratory assessments:
  - plasma HIV-1 RNA
  - CD4+ and CD8+ T-cells
- Recording of AIDS-defining events, non-AIDS severe events, and death

All patients having achieved a plasma viral load < 50 copies/ml at any time and having a subsequent viral load ≥ 50 copies/ml should be retested from 10 days to 4 weeks.

## **7.9 Assessment of treatments**

### **7.9.1 Antiretroviral treatment**

At all study visits, the following details are recorded for any antiretroviral drugs, including the study drugs:

- commercial name of the product
- formulation
- dosage per unit
- prescribed dosage
- start date of this prescribed dosage
- stop date of this prescribed dosage
- reason for discontinuation

#### **7.9.2 Concomitant treatment**

At all study visits, the following details are recorded for all concomitant medications:

- commercial name of the product
- formulation
- dosage per unit
- prescribed dosage
- indication
- start date
- stop date

### **7.10 Assessment of compliance and adherence**

Patient's compliance to treatment is assessed by the following procedures during the trial:

- self-questionnaire (see paragraph 7.5 for schedule of assessments)
- counting of returned drugs at the end of trial treatment

Patients' adherence to the trial is assessed by recording loss-to-follow-up, missed visits, and the reason for withdrawals. Effort should be made to contact patients who do not come to scheduled study visit and to obtain at least information on vital status.

### **7.11 Other assessments**

The following ancillary assessments are performed in all patients:

- Blood sampling for Pharmacogenetics study (in consenting patients)
- Blood sampling for Population pharmacokinetics
- Blood sampling for Viral sub-type study
- Blood sampling for Renal function study
- Self-questionnaire for Quality of life study
- Recording of in-patient care resource utilisation for Pharmacoeconomics study

For the full assessment items, please refer to appendices 9-14.

## 7.12 Study regimen termination

Study regimen termination is defined by the definite discontinuation of any component of the initially allocated study regimen for any reason. The decision on regimen discontinuation should be taken based on clinical decision criteria and standard of care, and not on the protocol endpoints. The reason for regimen discontinuation and the date of discontinuation must be recorded in case record form.

The patient should receive appropriate 2nd line antiretroviral treatment after trial regimen discontinuation, based on current guidelines, patient's history and condition as well as co-medications.

Study regimen modifications should not lead to patient withdrawal from the trial: Patients discontinuing their study regimen have to be followed-up according to the scheduled trial visits until the end of the trial and all data should be collected (under the condition that informed consent has not been withdrawn).

If a patient wishes to discontinue trial treatment at any moment, investigators should explain the importance of remaining on trial follow-up, or - failing this - of allowing routine follow-up data to be used for trial purposes.

### Regimen termination guidelines

Decision to discontinue a patient from the study regimen may be considered in the following circumstances:

- Insufficient virologic response:
  - HIV-1 RNA reduction < 1 log10 copies/ml at W04, W08, W12 or W18, or HIV-1 RNA ≥ 400 copies/ml at W24  
Any decision should only be taken after confirmation of the HIV-1 RNA level and after discussion with the regional CTU.
  - HIV-1 RNA ≥ 50 copies/ml by W48 (if suppression of HIV-1 RNA < 50 copies/ml never achieved).
- Confirmed rebound in HIV-1 RNA ≥ 50 copies/ml after initial suppression below 50 copies/ml.  
All patients having achieved a plasma viral load < 50 copies/ml at any time and having a subsequent viral load ≥ 50 copies/ml should be retested from 10 days to 4 weeks.
- Disease progression whilst on therapy.
- Withdrawal of patient consent.
- Unacceptable toxicity.
- Intercurrent illness which prevents further treatment, such as the need to start concomitant treatment with medication that is not compatible with the use of the study medications.
- Any change in the patient's condition, such as pregnancy, which justifies the discontinuation of treatment in the clinician's opinion.

### 7.12.1 Management in the case of insufficient virologic response

- Insufficient virologic response before W32  
Insufficient virologic response before W32 is defined as HIV-1 RNA reduction  $< 1 \log_{10}$  copies/ml at W04, W08, W12 or W18, or HIV-1 RNA  $\geq 400$  copies/ml at W24.

In that case, adherence problems should be addressed and HIV-1 RNA levels confirmed. Any decision to modify the initial randomised regimen should only be taken after discussion between the investigator and the regional CTU.

- Failure to achieve a viral load  $< 50$  copies/ml by W48  
If by W48 the patient has never achieved HIV-1 RNA  $< 50$  copies/ml, either because of high viral load at inclusion or because of adherence problems, which should have been addressed, regimen change is strongly recommended.  
In patients with HIV-1 RNA  $\geq 50$  copies/ml at W48, HIV-1 RNA level should be retested from 10 days to 4 weeks.

### 7.12.2 Management in the case of protocol-defined virologic failure

Protocol definition of confirmed virologic failure is occurrence of an HIV-1 RNA level  $\geq 50$  copies/ml in two consecutive measurements, the second one to be done from 10 days to 4 weeks at the latest, after virologic suppression (HIV-1 RNA  $< 50$  copies/ml) at any time.

All patients having achieved a plasma viral load  $< 50$  copies/ml at any time and having a subsequent viral load  $\geq 50$  copies/ml should be retested at the local laboratory from 10 days to 4 weeks.

The December 1 2009 version of guidelines from the U.S. DHHS Panel on Antiretroviral Guidelines for Adults and Adolescents [3] states that low level viremia between 50 and 200 copies/ml of HIV-1 RNA should not necessarily be considered as virologic failure or a reason to change treatment. A similar position is adopted by the European EACS guidelines, version 5, November 2009 [2]. Therefore, patients with viral loads between 50 and 200 copies/ml should continue their treatment regimen, unless there is a clear indication to change therapy, such as documented resistance or if the low-level viremia is prolonged. In such cases, investigators must contact their regional CTU to discuss any virological concern before changing/modifying regimens. It is recommended to change the regimen when the viral load is confirmed  $\geq 200$  copies/ml.

At first HIV-1 RNA  $\geq 500$  copies/ml at any time after visit W32, HIV-1 genotype is to be assessed in the local laboratory. In addition, 1 ml of plasma is to be stored and frozen at that timepoint (biobank). This sample may later be sent to the central laboratory for centralised genotypic analysis (see specific SOP on sample handling and shipment).

In any case, change of therapy is left at the discretion of the treating clinician after careful assessment of failure reasons and consequences (genotypic resistance testing). The decision on regimen discontinuation should be taken based on clinical decision criteria and standard of care, and not on the protocol endpoints. The patients should be offered an active antiretroviral combination (see 7.12.5) and follow-up be continued until completion of the trial.

### 7.12.3 Management in the case of disease progression

In case of disease progression, either AIDS-defining events or serious non-AIDS events, the treating physician decides whether treatment changes are indicated.

### 7.12.4 Management in the case of treatment limiting adverse events

The investigator should consider temporarily withholding therapy if the severity of the adverse experience is Grade 3 or above and/or if clinically indicated. Such decision to interrupt therapy should take into account the patient's baseline laboratory values and any concomitant medication or clinical condition that could be contributory. At the discretion of the investigator, therapy may generally be reinitiated when laboratory abnormalities or clinical adverse events return to near normal or to baseline values. If the adverse event is considered serious or if exposure to the study drug(s) poses additional potential significant risk to the patient, rechallenge is not recommended.

Whenever study drugs are permanently interrupted, i.e. for > 1 month, the regional CTU should be immediately notified.

A dosing interval adjustment of tenofovir/emtricitabine is recommended in all patients with creatinine clearance 30-49 ml/min (see SmPC). Tenofovir/emtricitabine should be permanently discontinued if creatinine clearance is < 30 ml/min.

#### - Management of rashes

In case of rash grade 3-4 possibly related to study drugs, therapy should be immediately and permanently discontinued.

Rash grade 3:

- diffuse macular, maculopapular, or morbiliform rash with vesicles or limited number of bullae OR
- cutaneous rash/reaction with superficial ulcerations of mucous membrane limited to one site OR
- cutaneous rash/reaction with at least one of the following: elevation of AST and/or ALT > 2 x the baseline value and at least > 5 x ULN; fever (> 38°C); eosinophils > 1000/mm^3; serum sickness like reaction.

Rash grade 4:

- Extensive or generalised bullous lesions OR
- Stevens-Johnson syndrome (SJS) OR
- Ulceration of mucous membrane involving 2 or more distinct mucosal sites OR
- Toxic epidermal necrolysis (TEN)
- Cutaneous rash/reaction with eosinophilia and systemic symptoms (DRESS)

Grades 2 to 4 rashes are regularly validated by the Endpoint Review Committee and reviewed by the Independent Data Monitoring Committee and the Trial Steering Committee.

All relevant details to categorise treatment-limiting adverse events including nature, type, severity, relation to study drugs, evolution, etc are recorded in the CRF.

Follow-up after drug discontinuation follows planned study visits, with an additional visit 4 weeks after drug discontinuation, with the main objective to assess evolution of the event that led to study drug termination.

#### **7.12.5 Second line antiretroviral regimens**

If the treatment allocated by randomisation is discontinued for virologic failure, disease progression or treatment-limiting adverse events, the patient should be offered a new antiretroviral regimen based on current guidelines after assessment of cause of discontinuation, and genotypic testing results in case of virologic failure.

### **7.13 Management in the case of pregnancy**

In case of suspicion of pregnancy during the trial, a pregnancy test should be performed immediately. Pregnancy must be notified to the regional CTU.

If a female participant becomes pregnant, all study drugs that are not recommended during pregnancy based on the latest SmPC must be discontinued. Women should receive regimens that are authorised during pregnancy. For female patients requiring a change in study medication due to pregnancy, this should be done after discussion with the Trial Management Team (TMT). All patients should resume the initial randomised treatment within 6 weeks after delivery.

Follow-up of all patients continues until the end of the trial. All pregnancies are followed to the final outcome.

### **7.14 Management in the case of suspicion of Immune Reconstitution Syndrome**

If Immune Reconstitution Syndrome (IRS) is suspected, a detailed assessment of its etiology should be conducted [37]. All data relevant to the IRS event need to be recorded in the CRF. All cases of IRS are reviewed by the Endpoint Review Committee.

### **7.15 Patient transfers**

For patients moving from the area, every effort should be made for the patient to be followed-up at another participating trial centre and for this trial centre to take over responsibility for the patient. Access to the patient CRF must be provided to the new site. The patient may have to sign a new consent form at the new site, and until this occurs, the patient remains under the responsibility of the original centre.

### **7.16 Discontinuation and withdrawal**

In consenting to the trial, patients are consenting to trial treatment, trial follow-up and data collection.

Particular situations, which may result in deviations from this stipulation, are detailed in the following chapters.

#### **7.16.1 Premature discontinuation from the study**

A patient prematurely discontinues from the study if:

- the patient withdraws informed consent (cf paragraph 7.16.2).
- the patient permanently refuses to come back to study visits
- the patient is lost to follow up (cf paragraph 7.16.3).
- the patient dies.

In case the patient discontinues the study prematurely, the end-of-study page of the CRF is completed.

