### **7.16.2 Withdrawal of consent**

Patients may voluntarily withdraw from the study for any reason at any time. When a patient withdraws his/her consent to participate in the study, no new information must be collected and recorded in the database after the date of withdrawal. Similarly, no samples must be collected after that date in the context of the research study.

Withdrawals of consent to participate in the study must be reported to the regional CTU as soon as possible (by fax and by letter). The investigator must document the date, reason and any answers given in response to the patient, in the patient's medical records.

If a patient explicitly states his/her wish not to contribute data to the study, the regional CTU should be informed in writing of the patient's decision.

Patients withdrawing from the trial without stating this wish have previously consented to follow-up in the trial, and data up to this time can be included in the trial if it is anonymised.

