## 9.2 Analysis of the primary endpoint

The primary outcome is time to clinical or virological failure as defined in section 3.2.

The primary outcome is analysed using the Kaplan Meier method to calculate the absolute difference in proportions and 95% confidence interval at 96 weeks.

If the upper limit of this confidence interval is less than 9% then this is taken as evidence that darunavir/r + raltegravir is non-inferior to darunavir/r + tenofovir/emtricitabine according to the non-inferiority margin specified in the design. If this upper confidence bound is less than 0% then this is considered as evidence of the superiority of darunavir/r + raltegravir relative to darunavir/r + tenofovir/emtricitabine. The results are summarised with the number and percentage of patients with at least one component of the primary endpoint and the number and percentage for each component. As a secondary analysis, the results are also summarised by the rate of the composite primary endpoint per 100 person years by treatment group, a treatment hazard ratio (HR: darunavir/r + raltegravir relative to darunavir/r + tenofovir/emtricitabine) estimated by a Cox proportional hazards model and a two-sided 95% confidence interval for the hazard ratio.

The primary analysis is by intention to treat and includes all randomised participants. Each participant's follow-up is calculated from randomisation until the first occurrence of any component of the primary endpoint, to a common closing date of the trial (estimated as 96

weeks after the last randomisation) for patients who do not experience any component of the primary endpoint, the date endpoint status was last known, or date of withdrawal of consent for participants who are lost to follow-up for the primary endpoint. Thus censoring because of loss to follow-up will be treated as being independent of the outcome (independent censoring).

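### Section 7.16.1 closes out patients who refuse study visits without carrying over the routine-data fallback of section 7.12, so obtainable endpoint data will probably be lost

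*Protocol*

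**What the plan says.** Section 7.16.1 lists four ways of leaving the study early: withdrawal of consent, loss to follow-up, death, and the case where "the patient permanently refuses to come back to study visits". Withdrawal and loss each point to their own subsection. Refusal of visits points to none. For all four the instruction is the same: "In case the patient discontinues the study prematurely, the end-of-study page of the CRF is completed".

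Section 7.12 takes a different line for patients who come off their regimen. They stay on the visit schedule and "all data should be collected (under the condition that informed consent has not been withdrawn"). If a patient wishes to stop trial treatment, the investigator is to stress the value of staying in follow-up or, failing that, "of allowing routine follow-up data to be used for trial purposes".

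New data are barred only in section 7.16.2, after withdrawal of consent: "no new information must be collected and recorded in the database after the date of withdrawal". For missed visits, section 7.10 asks sites to contact the patient and "to obtain at least information on vital status".

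Section 9.2 ends follow-up, for those lost to the primary endpoint, at "the date endpoint status was last known, or date of withdrawal of consent for participants who are lost to follow-up". It adds: "Thus censoring because of loss to follow-up will be treated as being independent of the outcome".

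**The concern.** A patient who will not attend study visits but stays in HIV care remains informative. Death, AIDS events, serious non-AIDS events and viral load, which make up the six components of the primary endpoint in section 3.1, would ordinarily appear in the clinic record. Section 7.16.1 files this patient beside those who are untraceable, dead or without consent, and the end-of-study page tells the site that recording is over.

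The trial is open-label, so refusal may follow dislike of the allocated regimen and may be related to both arm and outcome. Section 9.2 would censor such a patient as independent. In a non-inferiority comparison, failures missed more often in the raltegravir arm make that arm look closer to control than it is. No later analysis can restore data that were never recorded.

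**Working it through.** **1. The sections side by side, for a patient who refuses visits and has not withdrawn consent**

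- Consent: section 7.16 describes it as covering treatment, follow-up and data collection. The bar in 7.16.2 is not triggered, so collection is permitted.
- Wish to collect: section 7.12 states it, but for patients who want to stop trial treatment. That group overlaps with visit refusers and is not identical to them.
- Instruction to collect: 7.16.1 has none. Section 7.16.3 covers patients whose status is unclear, which a refuser in local care need not be. Section 7.10 reaches vital status at least, which is one of the six components.
- Event notification: sections 8.2.1 and 8.3.1(d) end the duty to notify serious adverse events 30 days after the last follow-up visit, apart from related events. AIDS and serious non-AIDS events are notified through the same system (8.2.3). For a refuser this can be read as ending 30 days after the last visit attended.
- Analysis: the date in 9.2 is when endpoint status was last known. It is not tied to a study visit, so routine values would count if recorded.

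The gap is therefore in collection, not in the censoring rule.

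**2. How the plan allows for loss**

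Inputs from section 9.1: 400 per arm, 20% control failure at W96, margin 9 points, 10% lost by W144, 85% power for the W96 difference.

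- Evaluable per arm: 400 × 0.90 = 360.
- Standard error: √(2 × 0.20 × 0.80 / 360) = 2.98 points.
- Power at no true difference: Φ(9/2.98 − 1.96) = 85.5%, against 85% stated.

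The stated power is reproduced when loss enters only as lost information, with no bias.

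- At a constant rate, 10% by W144 gives 1 − 0.9^(96/144) = 6.8% by W96, about 27 per arm. This is loss of every kind. The protocol gives no figure for refusers.

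**3. Possible size of the bias (illustration)**

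Let d be the share of the raltegravir arm censored for refusal. Let e be the excess of their true risk of failing between refusal and W96 over the risk of patients still followed in that arm. Kaplan-Meier gives refusers the risk of those still followed, so if the control arm has no such excess, the difference is understated by about d × e. Neither d nor e is in the protocol. The last column is Φ(d × e / 2.98 − 1.96), the approximate chance of declaring non-inferiority when the true difference is 9 points (nominal 2.5%).

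| d | e (points) | Understatement (points) | Chance of a false claim |
|---|---|---|---|
| 2% | 10 | 0.2 | 2.9% |
| 6.8% | 20 | 1.4 | 6.6% |
| 10% | 40 | 4.0 | 27% |

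The standard error uses 20% failure in both arms. With 20% and 29% it is √((0.20 × 0.80 + 0.29 × 0.71)/360) = 3.19 points, and the last column becomes 2.9%, 6.3% and 24%. If d and e are the same in both arms, the shifts cancel and the difference moves by about zero.

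**The case against.** The strongest reply is that nothing in the protocol forbids collecting these data. That is correct, and it limits the point in five ways.

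- A reader might infer that routine HIV-1 RNA and events are not collected from refusers. No section says so. The only bar follows withdrawal of consent, and data-management detail is left to procedures not shown. Non-collection is what 7.16.1's silence and the end-of-study page make likely.
- A reader might infer that 9.2 censors at the last study-visit value. It does not.
- A reader might see a direct contradiction between 7.12 and 7.16.1. Because the 7.12 fallback is worded for stopping treatment, the two can be read in sequence. What is missing is the link.
- A reader might take a fraction of the planned 10% loss as recoverable. Section 9.1 defines that 10% as endpoint status unknown at the end of the trial. Patients known through routine care fall outside it, and the protocol does not split it by cause. No recoverable amount can be derived.
- Routine data may recover less than hoped. Under 9.2, follow-up is censored at W18 if W18, W24 and W32 are all missed, even with later attendance, and at W32 if HIV-1 RNA is missing at both W32 and W40. Later values from an early refuser would then not count.

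Independent censoring is also the usual Kaplan-Meier assumption, and further sensitivity analyses may stand in an analysis plan not shown. Their absence is no part of this point. What remains is that 7.16.1 fixes a disposition rule which, followed as written, would probably give up endpoint data that consent allows and 7.12 seeks.

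**Conclusion.** The point holds as a gap in data collection. Section 7.16.1 treats refusal of visits without withdrawal of consent as the end of the study for that patient, and does not carry over the fallback in 7.12. The censoring rule in 9.2 is sound for the purpose, and the sample size is unaffected.

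The size is uncertain. The range of 0.2 to 4.0 points assumes that 2% to 10% of one arm refuse and that they carry 10 to 40 points of excess risk in that arm only. Putting all of the planned 6.8% loss down to refusal, with 20 points of excess, gives 1.4 points. Equal refusal and equal excess risk in both arms give about zero. The change is worth making because it is cheap and protects the primary comparison, not because a material bias has been shown.

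**What to change.** Reconcile 7.16.1 with 7.12:

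- Count permanent refusal of visits as leaving the study only if the patient also refuses use of routine data.
- Keep the others in the study. Record their routine HIV-1 RNA, vital status, AIDS events and serious non-AIDS events on the existing follow-up forms up to the common closing date. Section 7.6 already uses these forms for follow-up to standard of care after W96.
- Send their clinical events to the blinded Endpoint Review Committee as for any other patient.
- State how irregularly timed values map to the W18, W24, W32 and W40 rules in 9.2 and to the confirmation requirement in 3.1.

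The censoring rule in 9.2 needs no change. The cost is a few lines of text and limited chart abstraction. The drawback is that routine values come at irregular times, which is why the mapping has to be written down.
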